4.8.1 Analysis of the Conduct of the Study

The study proposed has a single arm, open label study to test the safety of IV tPA in stroke upon awakening. The null hypothesis (Ho) is that IV rt-PA in this population will have a symptomatic intracerebral hemorrhage rate of less than 6%.

The alternative hypothesis (Ha) is that IV rt-PA will have a symptomatic intracerebral hemorrhage rate of more than 10%, which would be unacceptably high.

This is a proof of concept study. We will obtain the frequency of the primary outcome (symptomatic intracerebral hemorrhage within the first 36 hours).

- - 1. Baseline Demographics

The sample size will be 20 patients, to assess the safety of rt-PA in this population. The number of patients with acute stroke treated at Johns Hopkins Hospital (JHH) and Johns Hopkins Bayview Medical Center (JHBMC) from February 1, 2008 to January 31, 2009 was 175 and 196 respectively. Assuming that 12% may present with stroke symptoms upon awakening and be eligible by CT criteria (Based on a retrospective evaluation of one year of stroke patients at JHH), with a rate of agreement to participate of 60%; this would yield 12 and 14 study subjects per year at JHH and JHBMC respectively. Based on this assessment, this study can be completed in one year.

- - 1. Safety Analysis

Because this study is designed to assess safety, the safety analysis is the same as the primary outcome analysis, which is the assessment of the rate of symptomatic intracerebral hemorrhage after IV rt-PA in patients that present to the ED within 4.5 hours of waking up with stroke. A DSMB (composed of one member independent of the investigator team) will conduct an analysis of the rate of symptomatic intracerebral hemorrhage by ECASS 3 criteria.

Symptomatic intracerebral hemorrhages (events) will be evaluated after each subject completes therapy. During the phase of the study in which there are 1-10 subjects enrolled, the study will stop at any point there are two events. During the phase of the study in which there are 11-20 subjects enrolled, the study will stop at any point if there are three events.

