Kelly-Hayes et al (Stroke 1995) reported data from the Framingham study suggesting that strokes are more than twice as likely to occur between 4 and 8 am, than in the previous four hours from midnight to 4 am. This suggests that many strokes that are discovered upon awakening have occurred in the early morning hours just prior to awakening. Todo and collaborators (Cerebrovasc Dis, 2006) compared CT findings in patients with acute stroke. They evaluated three groups: Patients with known time of onset within 3 hours, patients with stroke symptoms present upon awakening, and patients with unknown time of onset. They found that hypodensity in the CT was present most often in the group of patients without a known time of onset than in the other two groups, suggesting a similarity between patients waking up with stroke and patients presenting within 3 hours of onset, which could be interpreted as patients waking up with stroke symptoms having an onset of stroke within the 3 hour window.

Barreto et al (Stroke 2009) conducted a retrospective analysis of patients with wake up stroke treated with thrombolytic therapy. These patients had no significant excess symptomatic intracerebral hemorrhage and showed improved functional outcomes compared with patients with wake up stroke that were not treated with rt-PA in their case series. The mortality however was higher in the rt-PA treated group, this was interpreted as being an effect of selection bias favoring more severe strokes to receive thrombolytic therapy and the cause of death was related to failed recanalization rather than symptomatic intracerebral hemorrhage.

Potential Risk to Human Subjects

The main potential risk of testing IV rt-PA in patients with wake up stroke is symptomatic intracerebral hemorrhage. The goal of this learning phase study is to determine safety. If shown to be safe in terms of symptomatic intracerebral hemorrhage rate, a confirmatory trial will be done to demonstrate efficacy.

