2.0 OBJECTIVES

The primary objective of this study is to evaluate the safety of intravenous rt-PA in patients waking up with symptoms of acute stroke and presenting to the ED within 4.5 hours from awakening and having either a non-contrast head CT without hemorrhage and without hypodensity more than 1/3 of the MCA territory; or MRI demonstrating no hemorrhage, and with a DWI lesion no greater than 70mL and FLAIR without a well demarcated hyperintense lesion that is more than 1/3 of the MCA territory.

Phase II, safety study.

2.1 primary Endpoints

1. Symptomatic intracerebral hemorrhage (sICH) within 36 hours of treatment. We will collect data on symptomatic intracerebral hemorrhage by using the ECASS 3 criteria as well as the original NINDS IV rt-PA trial criteria for comparison.

- In ECASS 3 symptomatic intracerebral hemorrhage is defined as: Any extravascular blood in the brain or within the cranium associated with a clinical deterioration defined as an increase in 4 points on the NIHSS, or that lead to death and was identified as the predominant cause of neurological deterioration.
- In the original NINDS IV rt-PA trial symptomatic intracerebral hemorrhage is defined as: A hemorrhage not seen in previous CT scans and there was a suspicion of hemorrhage or any deterioration in neurologic status.

2.2 secondary Endpoints

1. Asymptomatic intracerebral hemorrhage occurring at any time during the study.
2. Symptomatic intracerebral hemorrhage by ECASS 3 and the original NINDS IV rt-PA trial criteria occurring at any time during the study.

3. Efficacy measures:

a. Modified Rankin score, NIHSS, Barthel index at 90 days

b. NIHSS at 24hrs

c. Mortality at 90 days.

- 1. STUDY DESIGN
  2. **DESCRIPTION OF THE STUDY**

Design:

The study proposed is a one arm, open label study. The aim is to test the safety of IV rt-PA in stroke upon awakening.

The null hypothesis (Ho) is that IV rt-PA in this population will have a symptomatic intracerebral hemorrhage rate of less than 6%.

The alternative hypothesis (Ha) is that IV rt-PA will have a symptomatic intracerebral hemorrhage rate of more than 10%, which would be unacceptably high.

Treatment Regimen:

IV rt-PA 0.9mg/kg, maximum of 90mg. Administered by the standard protocol: 10% of the dose by Intravenous bolus injection, followed by infusion of the remainder over 1 hour.

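### With the acceptable sICH rate as the null hypothesis and only 20 patients, the trial cannot show safety: at conventional exact levels even 0 of 20 does not exclude 10%

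*Protocol*

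**What the plan says.** The hypotheses appear twice in the protocol, in section 3.1 (Description of the Study, under Design) and in section 4.8.1. The null is: "The null hypothesis (Ho) is that IV rt-PA in this population will have a symptomatic intracerebral hemorrhage rate of less than 6" percent. The other side reads: "The alternative hypothesis (Ha) is that IV rt-PA will have a symptomatic intracerebral hemorrhage rate of more than 10%, which would be unacceptably high".

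The design is single arm: "The study proposed is a one arm, open label study". The text under Baseline Demographics in section 4.8 fixes the size: "The sample size will be 20 patients, to assess the safety of rt-PA in this population". The only arithmetic beside that number is a recruitment estimate. No alpha, sidedness, power, precision or success criterion is given.

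The planned analysis is descriptive: "We will obtain the frequency of the primary outcome (symptomatic intracerebral hemorrhage within the first 36 hours"). The one decision rule is under Safety Analysis: "During the phase of the study in which there are 1-10 subjects enrolled, the study will stop at any point there are two events". From subject 11 to subject 20 the limit is three events.

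The use of the result is stated in the Introduction, under Potential Risk to Human Subjects: "If shown to be safe in terms of symptomatic intracerebral hemorrhage rate, a confirmatory trial will be done to demonstrate efficacy".

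**The concern.** A test can give positive support only to its alternative hypothesis. Here the alternative is that the treatment is unacceptably hazardous, and the acceptable rate is the starting assumption. Under this pair, a finding of safety can mean only that the null was not rejected. The smaller the sample, the easier that is to achieve, whatever the true rate.

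The go-ahead for a confirmatory trial rests on that finding, and the endpoint is a potentially fatal bleed. If the study runs to 20 subjects without stopping, nothing in the protocol prevents that from being reported as safety shown, although the data would still be compatible with the rate the protocol calls unacceptable.

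**Working it through.** **Inputs from the protocol.** Null below 6% and alternative above 10% (3.1, 4.8.1). N = 20 in one arm (4.8, Baseline Demographics). Stop at 2 events in subjects 1–10 and at 3 events in subjects 11–20 (4.8, Safety Analysis).

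**Assumptions.** Alpha is not stated, so I use exact binomial methods at one-sided 2.5%, 5% and 10%. For the stopping rule I take the event count as cumulative and each outcome as known before the next subject is treated.

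**The plan's own figures.** The recruitment yield reproduces: 175 × 0.12 × 0.60 = 12.6 (stated 12) and 196 × 0.12 × 0.60 = 14.1 (stated 14) per year. N = 20 cannot be reproduced as a statistical sample size, because no error rate or precision is given.

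**Step 1: the best possible result against 10%.** If the true rate is 10%, P(0 of 20) = 0.9^20 = 0.122. The exact upper limit for 0 of 20 is 1 − α^(1/20):

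| One-sided α | Upper limit for 0/20 | Excludes 10%? |
|---|---|---|
| 10% | 10.9% | no |
| 5% | 13.9% | no |
| 2.5% (two-sided 95%) | 16.8% | no |

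Any event makes it worse. The one-sided 95% limits are 21.6% for 1/20 and 28.3% for 2/20. The smallest n at which zero events would exclude 10% solves 0.9^n ≤ α: 22, 29 and 36 at one-sided 10%, 5% and 2.5%.

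**Step 2: the test as written.** For X ~ Bin(20, 0.06), P(X ≥ 3) = 0.115, P(X ≥ 4) = 0.029 and P(X ≥ 5) = 0.006. A fixed-sample exact test of 6% therefore needs at least 4 events at one-sided 5% (also 4 at 10%, and 5 at 2.5%). The stopping rule ends the study at 3 events at the latest, so that rejection region is never reached.

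**Step 3: what the stopping rule does.** The rule is not triggered if there are 0 events in total, 1 in total, or 2 with at most one of them in the first ten subjects. The last case has 10 × 10 + 45 = 145 arrangements, so

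P(not triggered) = (1−p)^20 + 20p(1−p)^19 + 145p²(1−p)^18.

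| True rate p | 0 events | 1 event | 2 events | Not triggered | Stops |
|---|---|---|---|---|---|
| 6% | 0.290 | 0.370 | 0.171 | 0.832 | 0.168 |
| 10% | 0.122 | 0.270 | 0.218 | 0.609 | 0.391 |
| 15% | 0.039 | 0.137 | 0.175 | 0.351 | 0.649 |

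Read as a test of the stated null, the rule has a type I error of about 17% at 6% and a power of about 39% at 10%.

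**The case against.** The strongest reply is that this is a learning-phase study. Section 4.8.1 calls it a proof of concept and promises only the observed frequency, so the planned analysis is already estimation. Taking the acceptable rate as the null is also a recognised form for monitoring harm, and the gap from 6% to 10% can be an ordinary indifference zone. Much of this stands. The pair would be defensible as a harm-monitoring device, and neither the gap nor the absence of a named confidence interval is an error here, since an interval can be left to an analysis plan. What does not stand is the step to the Introduction's conclusion. An analysis plan could add an alpha or an interval, but it could not make N = 20 support that claim.

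A second reply is that alpha is unstated. That is correct. The exact result would turn only at a one-sided alpha of about 12.2% or more. Other one-sided 95% limits for 0/20 are 11.9% (Wilson) and 10.9% (mid-P), which still include 10%, and 9.0% (Jeffreys), which does not. The statement is therefore about conventional exact levels and is not absolute.

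There are four stronger readings that a reader might infer and that the documents do not support:

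- *Zero events would leave open the rate at which the wake-up arm cited in the Introduction was stopped.* That rate was 3/21 = 14.3%. At one-sided 95% the limit of 13.9% just excludes it, since (18/21)^20 = 0.046. Only the two-sided limit of 16.8% leaves it open.
- *The trial's power is that of a fixed 20-patient test needing 4 events.* The protocol specifies no such test, and the stopping rule would prevent it from running. The stopping probabilities are the relevant figures.
- *A fully enrolled trial can show at most 2 events.* A third event could occur in subject 20, with probability 126p³(1−p)^17 = 0.021 at a true 10%. The monitoring analysis also uses the ECASS 3 definition, so NINDS-defined events could be more numerous.
- *The design can tell us nothing in either direction.* The stopping rule can signal harm, though weakly at 10%.

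**Conclusion.** The concern holds in this form: the stated hypotheses, N = 20 and the planned safety conclusion do not fit together. The mismatch in direction is visible in the text and needs no assumption. The mismatch in size depends on a conventional exact level: at one-sided 2.5%, 5% or 10%, no outcome in 20 patients excludes the 10% rate that the protocol calls unacceptable. On the cumulative reading of the stopping rule, a trial with a true 10% rate still runs through without triggering it about six times in ten, so finishing is weak evidence of an acceptable rate. This affects what may be concluded from the primary endpoint and the stated condition for the next trial. It does not make the study worthless as an early look for harm.

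**What to change.** Keep N = 20 and the stopping rule, and change the wording in three places.

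1. **Sections 3.1 and 4.8.1.** Replace the hypothesis pair with an estimation objective: the sICH proportion within 36 hours in treated subjects, with an exact (Clopper–Pearson) 95% confidence interval. If hypotheses are kept, reverse them (null: rate of 10% or more; alternative: rate below 10%) and state that 20 subjects cannot reject that null at one-sided 5%.
2. **Section 4.8.** State what the design can deliver. Zero events in 20 excludes only rates above about 14% (one-sided 95%) or 17% (two-sided 95%). The stopping rule triggers with probability 17%, 39% and 65% at true rates of 6%, 10% and 15%. Give the assumptions behind these figures.
3. **Introduction, Potential Risk to Human Subjects.** Reword the condition for the confirmatory trial so that completing this study means no early harm signal was seen, and not that safety has been shown.

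The cost is protocol wording and a less favourable claim, with no extra patients. Keeping the stronger claim would need a larger trial. For example, excluding 10% at one-sided 5% with 80% power takes about 61 patients if the true rate is assumed to be 2%, and about 286 if it is 6%.

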4.8.4 Efficacy Analysis

a. Primary Endpoint

Symptomatic intracerebral hemorrhage within 36 hours of treatment is the main safety outcome measure in clinical trials of thrombolytic therapy in acute stroke and is the primary outcome measure for this trial. (The ATLANTIS, ECASS, and NINDS rt-PA Study Group Investigators (Lancet 2004), Hacke W, et al (NEJM 2008).)

We will use the symptomatic intracerebral hemorrhage definition from both ECASS 3 as well as the original NINDS IV rt-PA trial criteria for comparison.

- In ECASS 3 symptomatic intracerebral hemorrhage is defined as: Any extravascular blood in the brain or within the cranium associated with a clinical deterioration defined as an increase in 4 points on the NIHSS, or that lead to death and was identified as the predominant cause of neurological deterioration.
- In the original NINDS IV rt-PA trial symptomatic intracerebral hemorrhage is defined as: A hemorrhage not seen in previous CT scans and there was a suspicion of hemorrhage or any deterioration in neurologic status.

b. Secondary Endpoints

1. Asymptomatic intracerebral hemorrhage at any time during the study.

2. Symptomatic intracerebral hemorrhage at any time during the study.

3. Efficacy measures:

a. Modified Rankin score, NIHSS, Barthel index at 90 days

b. NIHSS at 24hrs

c. Mortality at 90 days.

4.9 Data Quality Assurance

All data collected will be kept in password-protected computers. Paper documents will be in secure locations. All data will be kept under the subject’s ID and will not be referenced to the subject’s identifiers. We will not destroy study data.

Data management at the clinical site and coordinating center will be conducted according to Good Clinical Practices.

Clinical sites will be monitored every 6 months to assure quality of the data, compliance with regulations and to verify source documents.

5. ASSESSMENT OF SAFETY

5.1 Specification of Safety Variables

Safety assessments will consist of monitoring and reporting adverse events (AEs) and serious adverse events (SAEs) that are considered related to **ACTIVASE**, all events of death, and any study specific issue of concern.

5.1.1 Adverse Events

An AE is any unfavorable and unintended sign, symptom, or disease temporally associated with the use of an investigational (medicinal) product or other protocol-imposed intervention, regardless of attribution.

This includes the following:

- AEs not previously observed in the subject that emerge during the protocol-specified AE reporting period, including signs or symptoms associated with ischemic stroke that were not present prior to the AE reporting period.
- Complications that occur as a result of protocol-mandated interventions (e.g., invasive procedures such as cardiac catheterizations).
- If applicable, AEs that occur prior to assignment of study treatment associated with medication washout, no treatment run-in, or other protocol-mandated intervention.
- Preexisting medical conditions (other than the condition being studied) judged by the investigator to have worsened in severity or frequency or changed in character during the protocol-specified AE reporting period.

5.1.2 Serious Adverse Events

An AE should be classified as an SAE if:

It results in death (i.e., the AE actually causes or leads to death).

It is life threatening (i.e., the AE, in the view of the investigator, places the subject at immediate risk of death. It does not include an AE that, had it occurred in a more severe form, might have caused death.).

It requires or prolongs inpatient hospitalization.

It results in persistent or significant disability/incapacity (i.e., the AE results in substantial disruption of the subject’s ability to conduct normal life functions).

It results in a congenital anomaly/birth defect in a neonate/infant born to a mother exposed to the investigational product.

It is considered a significant medical event by the investigator based on medical judgment (e.g., may jeopardize the subject or may require medical/surgical intervention to prevent one of the outcomes listed above).

5.2 Methods and Timing for Assessing AND Recording Safety variables

The investigator is responsible for ensuring that all AEs and SAEs that are observed or reported during the study, as outlined in Section 5.1.1, are collected and reported to the FDA, appropriate IRB(s), and Genentech, Inc. in accordance with CFR 312.32 (IND Safety Reports).

5.2.1 Adverse Event Reporting Period

The study period during which all AEs and SAEs must be reported begins after informed consent is obtained and initiation of study treatment and ends 90 days following the last administration of study treatment or study discontinuation/termination, whichever is earlier. After this period, investigators should only report SAEs that are attributed to prior study treatment.

5.2.2 Assessment of Adverse Events

All AEs and SAEs whether volunteered by the subject, discovered by study personnel during questioning, or detected through physical examination, laboratory test, or other means will be reported appropriately.

Each reported AE or SAE will be described by its duration (i.e., start and end dates), regulatory seriousness criteria if applicable, suspected relationship to **ALTEPLASE** (see following guidance), and actions taken.

To ensure consistency of AE and SAE causality assessments, investigators should apply the following general guideline:

Yes

There is a plausible temporal relationship between the onset of the AE and administration of **ALTEPLASE**, and the AE cannot be readily explained by the subject’s clinical state, intercurrent illness, or concomitant therapies; and/or the AE follows a known pattern of response to **ALTEPLASE**; and/or the AE abates or resolves upon discontinuation of **ALTEPLASE** or dose reduction and, if applicable, reappears upon re-challenge.

No

Evidence exists that the AE has an etiology other than **ALTEPLASE** (e.g., preexisting medical condition, underlying disease, intercurrent illness, or concomitant medication); and/or the AE has no plausible temporal relationship to **ALTEPLASE** administration (e.g., cancer diagnosed 2 days after first dose of study drug).

Expected adverse events are those adverse events that are listed or characterized in the Package Insert or current Investigator Brochure.

Unexpected adverse events are those not listed in the Package Insert (P.I.) or current Investigator Brochure (I.B.) or not identified. This includes adverse events for which the specificity or severity is not consistent with the description in the P.I. or I.B. For example, under this definition, hepatic necrosis would be unexpected if the P.I. or I.B. only referred to elevated hepatic enzymes or hepatitis.

5.3 Procedures for Eliciting, Recording, and Reporting Adverse Events

5.3.1 Eliciting Adverse Events

All patients enrolled will have a non-contrast head CT within 20-30 hours post treatment with ACTIVASE or if there is any change or deterioration in neurological status. Presence of hemorrhagic transformation in the CT will be classified as symptomatic if there is a concomitant deterioration in the patient’s neurologic status and as asymptomatic if there isn’t any change.

During the 24-hour, 36 hour and 90 days visit, adverse events will be elicited by asking for new symptoms, diagnosis, changes in health, since the last visit.

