Treatment will be initiated within 4.5 hours of awakening, with a preferred target door to needle time of 60 minutes or less from arrival to the ED (i.e. the 60 minute door to needle time is a goal but not required for enrollment since the national target for standard IV rt-PA door to needle time is less than 60 minutes in 50% of patients treated).

No antithrombotic medications in the first 24 hours. After that period, choice of antithrombotic medication will be at the discretion of the treating physician

Study Interventions:

Once the patient has agreed to participate and has signed the consent form, a subject ID number will be assigned. Prior to be enrolled in the study, all subjects will have received the following procedures/tests:

1. History and physical examination.
2. EKG, CBC, electrolytes, creatinine and BUN, PT and PTT.
3. Two intravenous catheters will be started.
4. A non-contrast CT scan of the brain or MRI of the brain per the standard of care protocol at the clinical site.

The subject will then receive open label rt-PA via IV catheter at a dose of 0.9mg/kg, 10% given as a bolus and the remainder given as a continuous infusion over one hour. The maximum dose is 90mg.

The study subject will be monitored in the ED until the completion of the rt-PA infusion, following the standard protocol for monitoring after rt-PA administration for acute stroke within 4.5 hours of onset. Once the infusion is completed, the subject will be transferred to the intensive care unit where the observation as per the standard clinical care protocol will be followed. Blood pressure and neurological status will be closely monitored as per protocol. Observation in the intensive care unit will be for a minimum of 24 hours. Subjects will be under the care of the admitting physician that may also be the study investigator.

A non-contrast head CT will be done between 20-30 hours after administration of rt-PA and at any time before or after if there is the clinical suspicion of hemorrhagic transformation or a decline in the subject’s neurological status. If this is the case, the investigator will be notified and after evaluation of the CT scan and the neurological examination and NIHSS, a primary outcome point will be adjudicated. We will use the symptomatic intracerebral hemorrhage definition from both ECASS 3 as well as the original NINDS IV rt-PA trial criteria for comparison.

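### The section 5.3.1 rule for asymptomatic ICH fits neither sICH definition, so some bleeds fall outside both the ECASS 3 and asymptomatic counts and others fall in both the NINDS and asymptomatic counts

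*Protocol*

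**What the plan says.** Section 2.2 lists "Asymptomatic intracerebral hemorrhage occurring at any time during the study" as a secondary endpoint. Sections 3.3.3 and 4.8.4 repeat it. None of the three says what makes a bleed asymptomatic.

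Symptomatic ICH is defined in two ways, in sections 2.1 and 4.8.4 and in the description of the study (3.1):

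- **ECASS 3:** extravascular blood "associated with a clinical deterioration defined as an increase in 4 points on the NIHSS". A second limb covers a fatal bleed judged to be the main reason for the decline.
- **NINDS:** "A hemorrhage not seen in previous CT scans and there was a suspicion of hemorrhage or any deterioration in neurologic status".

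Section 5.3.1, on eliciting adverse events, gives a separate rule for hemorrhagic transformation on CT. It "will be classified as symptomatic if there is a concomitant deterioration in the patient’s neurologic status". For the other class, the same sentence labels the bleed "as asymptomatic if there isn’t any change". This is the only place where the protocol says how a bleed comes to be called asymptomatic.

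For monitoring, the safety analysis section (4.8.3) says that the DSMB "will conduct an analysis of the rate of symptomatic intracerebral hemorrhage by ECASS 3 criteria".

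**The concern.** Section 5.3.1 is a third standard. Unlike ECASS 3, it has no NIHSS threshold. Unlike NINDS, it has no limb for suspicion of hemorrhage. A label from one standard is therefore set beside sICH counts from two others, and nothing ensures that each bleed lands in exactly one row.

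This trial exists to describe bleeding in 20 patients. A reader will naturally set the asymptomatic count beside each sICH count. If the classes leave gaps or overlap, the asymptomatic rate cannot be read with either sICH rate. Two investigators could also label the same CT differently, depending on whether they worked from 5.3.1 or from 2.1.

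**Working it through.** The protocol states no figure to reproduce, so the check applies the three written rules to the possible kinds of bleed.

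**Inputs**

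- ECASS 3 sICH (2.1): NIHSS rise of 4 points, taken as 4 or more, or death with the bleed as the predominant cause of deterioration.
- NINDS sICH (2.1): a new bleed with suspicion of hemorrhage or any deterioration. Section 4.1.2 requires baseline imaging without hemorrhage, so a bleed on post-treatment imaging is taken as new.
- Section 5.3.1: symptomatic with any deterioration, asymptomatic with no change.
- Coding choices: an NIHSS rise of 1 point or more, or death from the bleed, counts as deterioration.

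**Check:** for each kind of bleed, add the number of rows it enters. A clean classification gives 1 under each sICH definition.

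| New bleed after treatment | ECASS 3 sICH | NINDS sICH | 5.3.1 label | ECASS 3 sICH + asymptomatic | NINDS sICH + asymptomatic |
| --- | --- | --- | --- | --- | --- |
| NIHSS unchanged, no suspicion, not fatal | no | no | asymptomatic | 0 + 1 = 1 | 0 + 1 = 1 |
| NIHSS unchanged, suspicion, not fatal | no | yes | asymptomatic | 0 + 1 = 1 | 1 + 1 = **2** |
| NIHSS up 1 to 3, not fatal | no | yes | symptomatic | 0 + 0 = **0** | 1 + 0 = 1 |
| NIHSS up 4 or more | yes | yes | symptomatic | 1 + 0 = 1 | 1 + 0 = 1 |
| Death caused by the bleed | yes | yes | symptomatic | 1 + 0 = 1 | 1 + 0 = 1 |

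Two rows fail. The third row is the gap: a bleed with 1 to 3 points of worsening is too mild for ECASS 3 but is not asymptomatic under 5.3.1. The second row is the overlap: suspicion alone meets NINDS, while 5.3.1 calls the bleed asymptomatic.

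The protocol foresees the overlap case. The description of the study calls for an unscheduled CT "if there is the clinical suspicion of hemorrhagic transformation or a decline in the subject’s neurological status", so suspicion without decline is a trigger in its own right.

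**Size of one bleed:** 1/20 = 0.05, or 5 percentage points of the rate.

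**After the fix:** with the non-symptomatic class defined as the complement of each sICH definition, the two failing rows become non-sICH under ECASS 3 and sICH under NINDS. Each then sums to 1 under both definitions, as do the other rows.

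**The case against.** The strongest reply is that no worsening bleed disappears. The protocol reports sICH under both definitions, and NINDS counts any deterioration, so a bleed with 1 to 3 points of worsening is still in a reported sICH row. This stands. A reader might infer that the trial will understate total bleeding; that holds only for someone who ignores the NINDS row.

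It can also be said that the protocol lists no any-ICH endpoint and never says that sICH and asymptomatic ICH must add up. That is true, and it makes the overlap an inconsistency between two listed endpoints rather than an error in a stated total. It does not explain why the same bleed should be reported as symptomatic and as asymptomatic.

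Third, 5.3.1 sits among the adverse-event procedures, the endpoint lists do not cite it, and an analysis plan might refine it. But it is the only rule the protocol gives, and it conflicts with the protocol's own definitions. This is a stated contradiction, not detail left for later.

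A reader might go further and infer that a bleed in a patient whose NIHSS improved has no class, being neither a deterioration nor an absence of change. The text does not support resting anything on that. In its sentence, the absence of any change is most naturally read as the absence of deterioration, which makes such a bleed asymptomatic.

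Lastly, 5.3.1 sets no NIHSS rule, so a 1-point difference need not be judged a deterioration, and a symptom that raises suspicion might be judged a change. Either judgement would narrow the gap or the overlap. The protocol states neither.

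**Conclusion.** The point holds as a defect in one secondary safety endpoint. As written, the asymptomatic ICH count leaves a gap beside ECASS 3 sICH (non-fatal bleeds with 1 to 3 points of worsening) and an overlap with NINDS sICH (suspected bleeds without neurologic change). Each such bleed is 5 percentage points at N = 20. The documents give no basis for saying how often these bleeds will occur, so no frequency is claimed.

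A reader might infer that the primary result or the stopping rule is compromised. Neither is. The primary sICH counts keep their own definitions, the DSMB analysis names ECASS 3, and the two-event and three-event limits count symptomatic hemorrhages. The asymptomatic label feeds none of these.

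The conclusion rests on reading 5.3.1 literally and on counting a 1 to 3 point NIHSS rise as a deterioration. It is worth correcting because the trial's question is bleeding and the correction is cheap.

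**What to change.** Replace the classification sentence in 5.3.1 with a rule along these lines, and point to it from 2.2, 3.3.3 and 4.8.4: each ICH on post-treatment imaging is classified separately under ECASS 3 and under NINDS; under each, asymptomatic (non-symptomatic) ICH is any ICH that does not meet that definition's sICH criteria; any ICH is reported as the sum of the two classes. Each bleed is then counted once per definition.

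The cost is one sentence and three pointers. CT and NIHSS are already collected, so no new data, visits or patients are needed. There is a small downside: the ECASS 3 row will contain bleeds with 1 to 3 points of worsening, so its rate will be higher than under the present wording whenever such bleeds occur. Label that row 'ICH not meeting ECASS 3 sICH', so that a patient who worsened is not described as asymptomatic.
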